The garment-type ECG monitoring system using a dry electrode (hitoe^®^), newly developed by Toray Industries, Inc. (Toray), enables non-invasive 2-week continuous ECG monitoring. In fiscal year 2017, a study was performed at the Department of Cardiology of University of Tsukuba hospital to compare this system with Holter ECG using the conventional gel electrodes in concurrent ECG monitoring in 18 patients who underwent ablation treatment for AF (H29-88). Comparison of the results of automatic analysis of ECG data obtained using the dry electrodes (hitoe^®^) and those using the gel electrodes demonstrated that both types of electrodes had comparable detection rates of various types of arrhythmia, including AF episodes differing in duration, etc. Since this suggests that the garment-type 2-week ECG monitoring system using the dry electrodes (hitoe^®^) is likely to offer a highly useful tool for diagnosis of post-ablation AF recurrence, the present study was planned. In addition, the garment-type ECG monitoring system, which can be easily put on and taken off, allows bathing during the monitoring period, and is also expected to reduce skin symptoms, as those associated with conventional adhesive gel electrodes, through the employment of the dry electrodes (hitoe®), which are made of highly hydrophilic polyester nanofiber.

1. **Objectives**

The objective of the study is to investigate, in a randomized crossover design, whether the garment-type 2-week Holter ECG monitoring system provides higher AF detection rate compared to the conventional 24-hour Holter ECG monitoring system for diagnosis of post-ablation AF recurrence.

1. **Description**
   1. Endpoints
      1. Primary endpoint

Detection rate of patients with recurrent AF (atrial fibrillation lasting at least 30 seconds)

- - 1. Secondary endpoints
- ECG acquisition rate: (total recording time – noise recording time)/total recording time
- Device comfort while wearing (questionnaire: attachment)
- Incidence of non-AF arrhythmia events
  1. Study Design

Open-label, crossover, block-randomized controlled trial

- 1. Study Schema (flowchart)

[figure not shown]

1. Primary endpoint

🞄 Recurrent AF detection rate

2. Secondary endpoints

i. ECG acquisition rate

ii. Wearing comfort (questionnaire)

iii. Incidence of non-AF arrhythmia

Three months post-ablation

hitoe wear

(14 days)

hitoe wear

(14 days)

Conventional Holter

(24 hours)

Conventional Holter

(24 hours)

<Potential participants>

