- 1. Planned Duration of Patient Participant and Follow-up Period

After catheter ablation, informed consent will be obtained from potential participants. Those who satisfy all of the inclusion criteria and none of the exclusion criteria will be enrolled in the study, and an appointment for long-term ECG monitoring 3 months post-ablation will be arranged for them. Patients will undergo two different types of long-term ECG monitoring for a total of 15 days according to the assigned sequence and will be asked to answer a questionnaire when returning their ECG devices and observed for occurrence of adverse event, at the end of their participation in the study.

- 1. Study Termination, Discontinuation, and Interruption
     1. Study termination

At the end of the study, the investigator will publish the results in the Japan Registry of Clinical Trials (jRCT) by promptly submitting a notification of study termination to the Minister of Health, Labour and Welfare. The termination notification shall be prepared using Attached Form 1, “Notification of Trial Termination Notice," available on the website of the Ministry of Health, Labour and Welfare (MHLW).

- - 1. Study discontinuation/interruption
- The investigator shall consider whether to continue the study or not if any of the following are satisfied:

1) Any significant information regarding the quality, safety, or efficacy of the study devices becomes available

- - - 1. Any fact or information that compromises the properness or reliability of the study conduct becomes available
      2. It is judged difficult to recruit sufficient number of patients to achieve the planned sample size
      3. The study objectives are achieved prior to achievement of the planned sample size or planned duration, or it is judged that expected results cannot be obtained
      4. The certified review board (CRB) requests that the study protocol, etc. be changed and it is judged difficult to accept the request
    1. Policy of measures to be taken for patients after study discontinuation/termination

ECG monitoring may be performed after study discontinuation or termination at the discretion of the treating physician or at the patient's request.

- Upon decision to discontinue the clinical study, the investigator shall take the following actions:

1. Notify the CRB and the Minister of Health, Labour and Welfare within 10 days after the day of discontinuation.

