- - 1. Safety analysis set

All subjects except those who have no post-randomization data available

- 1. Analysis Items and Methods
     1. Level of significance and level of confidence

For statistical hypothesis test, a significance level of 0.05 for a two-sided test and 95% confidence interval (CI) will be used.

- - 1. Patient demographics analysis

The frequency or mean and standard deviation will be calculated as appropriate for sex and age.

- - 1. Primary analysis of the primary endpoint

An exact McNemar's test will be performed.

- - 1. Other analyses of the primary endpoint

The percentage and its exact CI will be determined for each device.

- - 1. Secondary endpoint analysis

Binary variables of the secondary endpoints will be analyzed as with the primary endpoint. For frequency variables, basic statistics (mean, standard deviation, median, and interquartile range) will be determined and analyzed by Wilcoxon rank sum test.

- - 1. Safety endpoint analysis

The safety endpoint will be analyzed as with the primary endpoint.

- - 1. Handling of dropouts

In efficacy analysis, test of binary variables will be performed with missing data of dropouts replaced with “absent” for both devices if no data are available for either device, and with “present” for both devices if the result for one device is available and is “present.” For other analyses, no specific processing or imputation or modeling for missing values will be performed.

1. **Source Data Verification**

The investigator and study site shall allow direct access to all study-related records, including source documents, etc., for study-related monitoring and auditing as well as inspections by the CRB and regulatory authorities.

1. **Quality Control and Quality Assurance**

The investigator shall entrust the monitoring and auditing operations to a contract research organization (CRO) to ensure the reliability of the conduct and recording of the study. The investigator and study site shall cooperate with the CRO in monitoring and auditing. The investigator shall inform potential participants in writing that the source documents will be disclosed to monitors and auditors and obtain written consent to such disclosure from the potential participants.

- 1. Monitoring Methods

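### If non-AF arrhythmia is compared as event counts, a 14-day total is tested against a 24-hour total by an unpaired test; the ECG acquisition rate does not show scheduled time lost to early stopping

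*Protocol*

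**What the plan says.** Under Secondary endpoints the Protocol lists "Incidence of non-AF arrhythmia events". It gives no unit or time denominator and does not say whether the variable is a count or a yes/no result per patient. The same list defines "ECG acquisition rate: (total recording time – noise recording time)/total recording time".

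Secondary endpoint analysis sends binary variables to the primary method (exact McNemar). For the rest it says "For frequency variables, basic statistics (mean, standard deviation, median, and interquartile range) will be determined", followed by a Wilcoxon rank sum test. It mentions no scaling by recording time, no offset and no matched window.

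The recording windows are fixed and unequal. The Objectives ask "whether the garment-type 2-week Holter ECG monitoring system provides higher AF detection rate compared to the conventional 24-hour Holter ECG monitoring system", and the section on planned duration says "Patients will undergo two different types of long-term ECG monitoring for a total of 15 days", that is 14 + 1. Every patient wears both devices.

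The background says that the garment "can be easily put on and taken off, allows bathing during the monitoring period". It does not say whether the recorder runs while the garment is off.

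**The concern.** A count grows with the time over which it is taken. If frequency means number of events, the planned test sets about 336 h of recording against 24 h. A significant result would then be close to certain even if both devices detected arrhythmia equally well per hour, and it could be read as a property of the garment. The rank sum test is also built for two independent groups, whereas these are two measurements on each patient.

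The acquisition rate raises a different and smaller matter. Its denominator is the time actually recorded. Time that was scheduled but never recorded appears in neither the numerator nor the denominator, so the measure can stay high while much of the 14 days is missing. Lost recording time is an obvious practical risk of long wear: the Protocol itself anticipates skin reactions with long-term use and provides for withdrawal because of adverse events.

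**Working it through.** **1. The plan's own figure.** The only relevant stated figure is the minimum sample size of 68. The inputs, from Target Sample Size and Rationale for Setting, are a 1-day risk of 0.05, a 14-day risk of 0.171 and a correlation of 0.460.

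- Both positive: 0.05 × 0.171 + 0.460 × √(0.05 × 0.95 × 0.171 × 0.829) = 0.0463.
- Discordant cells: 0.171 − 0.0463 = 0.1247, and 0.05 − 0.0463 = 0.0037.
- Power of the two-sided exact McNemar test at 0.05: 0.793 at N = 67, 0.803 at N = 68 and 0.822 at N = 70.

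The figure of 68 reproduces. This point does not touch it.

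**2. Event counts with identical devices.** The window ratio is 336 h / 24 h = 14. Assumptions: 70 patients; each patient's daily rate drawn from a gamma distribution (shape 0.3 or 1); Poisson counts at the same rate on both devices; two-sided 0.05. The event rates are assumed because the Protocol gives none. Runs were 1000 per scenario, or 2000 for the last two rows. Any rejection is a false signal of a device difference.

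| Comparison | Mean ≤ 1 event/day | Mean ≥ 5 events/day |
|---|---|---|
| Raw 14-day vs 1-day totals, rank sum | 100% | 100% |
| Divided by days, rank sum | 51 to 100% | 0 to 2% |
| Divided by days, signed-rank | 11 to 73% | 5 to 7% |
| Matched 1 day vs 1 day, rank sum | 0.1 to 4.2% | 0% |
| Matched 1 day vs 1 day, signed-rank | 4.1 to 5.4% | 4.0 to 4.5% |
| 14 days vs 1 day, paired Poisson comparison with recording-time offset and robust variance | 4.4 to 7.9% | 4.1 to 5.0% |

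Three things follow.

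- Unscaled totals always differ.
- Dividing by days does not repair a rank test when events are rare. A 14-day average and a single-day count have differently shaped distributions even when their means agree.
- With equal windows the rank sum test falls well below 5%. This is the cost of ignoring the pairing: it loses power to see a real difference.

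**3. Yes/no occurrence with identical devices.** For a daily probability q with independent days (assumed), the 14-day probability is 1 − (1 − q)^14. Exact McNemar at N = 70 gives:

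- q = 0.02: 2.0% vs 24.6%, power 0.986.
- q = 0.05: 5.0% vs 51.2%, power about 1.0.
- q = 0.95: nearly everyone is positive on both devices, power 0.14.

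The binary form is therefore often significant through duration alone, but not always.

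**4. Acquisition rate.** Assume 5% noise and a recorder that is not running for the lost time. The Protocol's formula gives 95% in every row below.

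| Lost time | Clean time / scheduled 336 h |
|---|---|
| 1 h/day off | 0.95 × 23/24 = 91.0% |
| 4 h/day off | 0.95 × 20/24 = 79.2% |
| 10 of 14 days recorded | 0.95 × 10/14 = 67.9% |
| Stopped after day 7 | 0.95 × 7/14 = 47.5% |

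The last two rows hold whenever recording has ended. The first two hold only if the recorder stops during removal. If it keeps running, off-body time stays in the denominator and would presumably count as noise, and the formula would then show the loss.

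**The case against.** The strongest case on the other side has four parts.

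- **Counts are never named as the variable.** Incidence could mean yes/no per patient, or a rate defined in an analysis plan that is not shown. This stands, so the point is conditional on counts. It does not remove the point, because the Protocol itself fixes the test for frequency variables. That test is unsuited to paired data, and it is badly misleading if applied to raw totals.
- **Unequal duration is the trial's intended contrast.** This also stands for the yes/no form. A 14-day against 24-hour yield compares two monitoring strategies, exactly as the primary endpoint does. A reader might infer that the arrhythmia comparison cannot fail to be significant, or that its null is false by construction in every form. The documents do not support that. The Protocol's own sample-size model fails about one time in five at N = 68, and a very common arrhythmia would leave little to detect.
- **The acquisition rate is a proportion of each device's own recording.** It has no 14:1 problem and speaks to ECG quality, which the background names as a weakness of external recorders. This stands. A reader might infer that the formula favours the garment whatever its performance. It does not: a noisier garment scores lower, and whether removal is hidden depends on recorder behaviour that is not stated.
- **Lost wear also reduces AF yield on the primary endpoint.** It is therefore not wholly invisible to the trial. This is true, but the primary result would not show how much scheduled time was lost.

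**Conclusion.** The point holds in a limited form. If event counts are compared, the stated rule tests a 14-day total against a 24-hour total with an unpaired test, and two identical devices would almost surely differ (100% of simulated runs, under assumed gamma-Poisson rates of 0.1 to 50 events per day). If the endpoint is yes/no, the comparison is legitimate as diagnostic yield and wrong only if read as a device difference.

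The acquisition formula is not an error. It measures the quality of what was recorded, not coverage of what was scheduled. It misses lost coverage for certain only when a patient stops early; for temporary removal the Protocol leaves the matter open. The 95% against 68% example rests on an assumed 5% noise and 10 of 14 days recorded.

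Both matters concern secondary endpoints. The primary analysis and the sample size of 68 are unaffected.

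**What to change.** - State whether non-AF arrhythmia is analysed as a count, as yes/no, or as both, and give each its time base.
- For any frequency comparison between devices, use a matched 24-hour garment window (for example the first 24 h) against the 24-hour Holter, with the Wilcoxon signed-rank test. Alternatively, use a paired count model with log analysable recording time as offset. Do not rely on division by days followed by a rank test.
- Report yes/no occurrence over 14 days versus 1 day as diagnostic yield of the two monitoring strategies, not as a device difference.
- Keep the acquisition rate as signal quality while recording. Beside it, report noise-free time divided by scheduled time (336 h garment, 24 h Holter), and state whether the recorder runs while the garment is off.

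The cost is definition wording and a little more analysis work. Recording time and noise time are already needed for the present formula. Event counts by time window are not listed as captured data, so their availability from the ECG analysis should be confirmed. The garment's coverage figure may look less flattering than its present acquisition rate.

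### The Wilcoxon rank sum test named for numeric secondary endpoints ignores the pairing in this crossover; with positive within-patient correlation it is too conservative and loses power

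*Protocol*

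**What the plan says.** The Study Design heading describes an "Open-label, crossover, block-randomized controlled trial". The section on planned duration of participation adds: "Patients will undergo two different types of long-term ECG monitoring for a total of 15 days according to the assigned sequence". Each patient therefore supplies one result per device.

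Under Analysis Items and Methods, the primary endpoint is handled with a paired test: "An exact McNemar's test will be performed". For the secondary endpoints, "Binary variables of the secondary endpoints will be analyzed as with the primary endpoint", so these are also analysed as pairs. The next sentence covers the rest: "For frequency variables, basic statistics (mean, standard deviation, median, and interquartile range) will be determined and analyzed by Wilcoxon rank sum test". The general testing rule is that "a significance level of 0.05 for a two-sided test and 95% confidence interval (CI) will be used".

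Two listed secondary endpoints may fall under the rank sum rule. One is "ECG acquisition rate: (total recording time – noise recording time)/total recording time", a ratio for each patient and device. The other is "Incidence of non-AF arrhythmia events", if it is analysed as a count and not as present or absent.

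**The concern.** The rank sum test takes its null variance from two unrelated samples. Here the two samples are the same patients measured twice. If a patient's two values are positively correlated, the difference between devices varies less than the test assumes, so p-values come out too large and real differences are more easily missed. If the correlation is negative, the error runs the other way.

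The sentence is also out of step with the rest of the plan. Pairing is used for the primary endpoint and the binary secondary endpoints, and the sample size calculation includes a within-patient correlation of 0.460. Only the numeric endpoints lose it.

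At stake is mainly ECG acquisition rate, the trial's measure of signal quality. The background section cites poor ECG quality as one reason for the high false-positive rate of external loop recorders. A test that is too conservative tilts this comparison towards no significant difference between the dry and gel electrodes.

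**Working it through.** **Step 1. The plan's own figure, which depends on the pairing.** Inputs from Target Sample Size and Rationale: 14-day risk 0.171, one-day risk 0.05, correlation 0.460. Two-sided 0.05 comes from the significance-level section.

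- Both positive: p11 = 0.171 × 0.05 + 0.460 × √(0.171 × 0.829 × 0.05 × 0.95) = 0.00855 + 0.03775 = 0.0463.
- Garment only: p10 = 0.171 − 0.0463 = 0.1247.
- Holter only: p01 = 0.05 − 0.0463 = 0.0037.
- Discordant pairs: Binomial(n, 0.1247 + 0.0037 = 0.1284), then a two-sided exact binomial test on the split.
- Unconditional power: 0.793 at n = 67, 0.803 at n = 68, 0.822 at n = 70.

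The stated minimum of 68 is reproduced exactly. The primary analysis is correctly paired and correctly sized.

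**Step 2. Size of the rank sum test on paired data.** In large samples, with Spearman correlation ρs between the two devices' values, the variance of the rank sum statistic is (1 − ρs) times what the test assumes. Hence

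size ≈ 2 × [1 − Φ(1.96 / √(1 − ρs))], where for normal data ρs = (6/π) × arcsin(ρ/2).

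Worked case, ρ = 0.3: ρs = 0.2876, √(1 − 0.2876) = 0.844, 1.96 / 0.844 = 2.322, size = 2.0%.

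The Protocol gives no ρ for the numeric endpoints, so a range is assumed. The simulated sizes use 70 bivariate-normal pairs, nominal two-sided 5%.

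| Assumed ρ | Formula | Simulated |
|---|---|---|
| −0.3 | 8.4% | 9.2% |
| 0 | 5.0% | 4.7% |
| 0.3 | 2.0% | 2.2% |
| 0.5 | 0.6% | 0.8% |
| 0.7 | 0.05% | 0.1% |

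At ρ = −0.3, separate simulation runs gave 8.3% to 9.2%, hence 8–9%. In runs with 68 pairs, the signed-rank test kept a size between 4.2% and 5.9% for all correlations from −0.3 to 0.8.

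**Step 3. Power for a shift of 0.3 SD.**

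| Assumed ρ | Rank sum | Signed-rank |
|---|---|---|
| 0 (68 pairs) | 40% | 40% |
| 0.3 (70 pairs) | 39% | 54% |
| 0.5 (70 pairs) | 39% | 68% |
| 0.7 (70 pairs) | 35% | 87% |

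Repeat runs put the rank sum figure at ρ = 0.5 between 36% and 39%. Rank sum power stays roughly flat as the correlation rises, while signed-rank power roughly doubles. That gap is the precision the crossover offers and the named test does not use.

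**The case against.** **The figures rest on an unknown correlation.** This stands. The 0.460 in the sample size section concerns AF detection, not signal quality or arrhythmia counts. The two recordings use different electrodes, leads, recorders and software, and are made on different days, so the correlation of acquisition rate could be low. At zero correlation nothing is lost. Acquisition rate is also bounded at 1 and counts are likely to be skewed, whereas the simulation used normal data. The figures illustrate the mechanism and do not estimate the loss in this trial.

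**The scope is inferred.** This stands too. The sentence speaks of frequency variables. That acquisition rate is included follows from the mean, SD, median and IQR listed and from the absence of any other test for it. If non-AF arrhythmia is scored as present or absent, the paired test already applies.

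**A rank sum test can be valid in a crossover.** It can, if within-patient period differences are compared between the two sequence groups. The Protocol mentions neither period differences nor a comparison of sequences, so this does not rescue the wording. It does mean that there is more than one acceptable correction.

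**The detail may be left to the SAP.** This does not stand for the choice of test, because the Protocol names one.

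**Stronger readings that the document does not support.** A reader might infer that false-positive claims are the main danger; that needs negative correlation, which is not the expected direction here. A reader might also infer that event counts over 14 days will be ranked against counts over 24 hours without adjustment. The Protocol neither states nor excludes a rate per recording time, that derivation can be left to the SAP, and the trial compares unequal windows on purpose for its primary endpoint. It is not part of this point.

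**Conclusion.** The rule is wrong as written: an independent-groups test is named for paired data, beside a sentence that treats the binary endpoints as pairs. With positive within-patient correlation the consequence is conservatism. Over an assumed range of 0 to 0.7, with 70 pairs of normal data, true size falls from about 5% to about 0.1%, and power for a 0.3 SD shift is about 35–40% against 40–87% for the signed-rank test. A negative correlation would make the test anti-conservative, at 8–9% for −0.3.

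Only numeric secondary endpoints are affected. The exact McNemar analysis, the binary secondary endpoints and the sample size of 68 stand. This should be fixed before analysis, but it does not threaten the primary conclusion.

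**What to change.** In Secondary endpoint analysis, replace the rank sum test with the Wilcoxon signed-rank test on the within-patient difference (hitoe minus Holter), preferably with a Hodges–Lehmann estimate and 95% CI. Alternatively, keep the rank sum test and state that it compares within-patient period differences between the two sequence groups. Either is acceptable. It would help to say in the same sentence which secondary endpoints the rule covers.

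The cost is one amended sentence in the Protocol, carried into the SAP if there is one. No new data, no extra patients and no change to the primary analysis are needed.

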3. Holter ECG is scheduled 3 months after ablation at University of Tsukuba Hospital
4. Consented to 14-day wearing of the garment-type ECG system
5. Underbust size in the range of 60 to 120 cm (3 wear sizes: S, M, and L available)
   1. Exclusion Criteria
6. Predisposition to allergy
7. History of such skin conditions as redness, erosion, and scarring due to adhesive sensitivity
8. Use of a pacemaker or electrical defibrillator

(This is set because a pacing pulse detector is not built in)

- 1. Withdrawal Criteria

1. The patient’s refusal to participate in the study or withdrawal of his/her consent to participate in the study
2. Discovery after enrollment that the patient is not eligible for participation in the study
3. Inappropriate for the patient to continue participation in the study due to aggravation of the underlying disease
4. Difficult for the patient to continue participation in the study due to aggravation of a complication
5. Difficult for the patient to continue participation in the study due to adverse event
6. Discontinuation of the entire study
7. Appropriate, in the opinion of the investigator, for the patient to discontinue participation in the study for other reason
8. **Intervention**
   1. Evaluation Schedule

For the present study, evaluation of recurrent AF by garment-type 2-week ECG monitoring and conventional 24-hour ECG monitoring is relevant to this section. Patients will be tested according to the randomized assignment in the period from 3 months post-ablation, when periodic monitoring for AF recurrence is scheduled, following the schedule in the table below.

| **<Conventional Holder ECG first>** | **<hitoe wear ECG first>** |
| --- | --- |

| Item | | Preparation for test | Testing period | | |
| --- | --- | --- | --- | --- | --- |
| Time | | 1 to 3 months before test | Day 0 | Day 14 | Day 15 |
| Informed consent | | ○ |  |  |  |
| Underbust measurement | | ○ |  |  |  |
| Patient enrollment (randomization) | | ○ |  |  |  |
| ECG appointment | | ○ |  | ● | ● |
| Monitoring for adverse event ^a^ | |  |  | ● | ● |
| ECG | Conventional Holter |  |  |  |  |
|  | hitoe wear |  |  |  |  |

| Item | | Preparation for test | Testing period | | |
| --- | --- | --- | --- | --- | --- |
| Time | | 1 to 3 months before test | Day 0 | Day 1 | Day 15 |
| Informed consent | | ○ |  |  |  |
| Underbust measurement | | ○ |  |  |  |
| Patient enrollment (randomization) | | ○ |  |  |  |
| ECG appointment | | ○ |  | ● | ● |

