| Monitoring for adverse event ^a^ | |  |  | ● | ● |
| ECG | Conventional Holter |  |  |  |  |
|  | hitoe wear |  |  |  |  |

○ Indicates the items to be performed before ECG start, and ● indicates those to be performed after ECG start.

a: Adverse event is any untoward event, including adverse reaction, regardless of whether it has a causal relationship with the device.

- 1. Contraindications

Do not wear a study device while undergoing magnetic resonance imaging (MRI). Local heat due to induced electromotive force may cause burns.

- 1. Concomitant Use of a Topical Medicine

Use of a topical medicine for skin pruritus will be acceptable.

1. **Efficacy Evaluation**
   1. Efficacy indicator

- Presence of atrial fibrillation lasting for at least 30 seconds
  1. Methods and Timing of Evaluation, Recording, and Analysis

In evaluation of post-ablation AF, the definition of AF recurrence has been established as atrial fibrillation lasting for at least 30 seconds. The acquired ECG data will be automatically analyzed, and the analysis results will be entered in each patient’s electronic medical record. The data will be locked to evaluate the efficacy indicator when data from all 70 patients are accumulated or 6 months after the end of the patient enrollment period, whichever comes earlier.

1. **Safety Evaluation**
   1. Safety indicator

- Presence of skin redness, erosion, or scarring
  1. Methods and Timing of Evaluation, Recording, and Analysis

The safety indicator was set since long-term use of the garment device may cause redness, skin erosion, and rarely scarring at the device contact area in patients with sensitive skin (with a predisposition to allergy) (refer to the package insert). Before removing the study device, a clinical laboratory technologist and a clinical research coordinator (CRC) will conduct a questionnaire (separate sheet) and observe the device contact area, and patients with suspected skin disorder at the device contact area will be seen by a physician.

- 1. Procedures for Information Gathering, Recording, and Reporting on Adverse Events
     1. Preparation of procedures for taking measures in the adverse event

1. The investigator shall prepare procedures for taking actions in the adverse event for each protocol, and act as specified in the procedures.

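### The paired skin-safety test loses any garment-first patient who is withdrawn for a garment reaction before the Holter, which biases that test towards no garment disadvantage

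*Protocol*

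**What the plan says.** All references are to the Protocol.

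- **Safety indicator** (Safety Evaluation): "Presence of skin redness, erosion, or scarring", a binary outcome.
- **Safety endpoint analysis** (Statistical Design): "The safety endpoint will be analyzed as with the primary endpoint".
- **Primary analysis of the primary endpoint**: "An exact McNemar's test will be performed".
- **Other analyses of the primary endpoint**: "The percentage and its exact CI will be determined for each device".
- **Handling of dropouts**: an imputation rule is given for binary tests in efficacy analysis. Then: "For other analyses, no specific processing or imputation or modeling for missing values will be performed".
- **Safety analysis set**: "All subjects except those who have no post-randomization data available". A patient with garment data only is therefore kept in the set.
- **Withdrawal Criteria**: one criterion reads "Difficult for the patient to continue participation in the study due to adverse event".
- **Patient Enrollment and Assignment**, and **Evaluation Schedule**: patients are randomized to garment first or Holter first. In the garment-first sequence the 24-hour Holter comes after the 14 days of wear.
- **Expected adverse reactions and expected defects**, repeated under **Safety Evaluation**: redness, erosion and occasionally scarring are singled out as possible results of prolonged garment wear in sensitive skin.

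**The concern.** McNemar's test draws its information only from patients who react on one device and not on the other, so it needs both results. The Protocol applies that test to the skin endpoint and fixes that missing values are not handled outside efficacy. The loss described here therefore follows from rules the Protocol sets and is not a detail left to a later document.

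Consider a garment-first patient whose skin reaction leads to withdrawal before the Holter. The garment result is present and the Holter result is missing. The safety set keeps this patient, but the paired test cannot use the data. The missing value is caused by the reaction itself. In the Holter-first sequence the Holter result already exists when the garment is put on, so a garment reaction cannot be lost in this way.

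The structure copied from the primary endpoint places McNemar as the main analysis and the percentages among the other analyses. A non-significant p-value could then be read as no skin disadvantage when some of the more troublesome garment reactions were outside the comparison.

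**Working it through.** **1. Check of the test against the plan's own figure.** The Protocol gives no figure for the safety test, but it does for the same test on the primary endpoint: 68 patients for power of at least 0.8. Inputs from Target Sample Size: 14-day risk 0.171, one-day risk 0.05, correlation 0.460.

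- P(both) = 0.171 × 0.05 + 0.460 × √(0.171 × 0.829 × 0.05 × 0.95) = 0.0463
- Garment-only = 0.171 − 0.0463 = 0.1247; Holter-only = 0.05 − 0.0463 = 0.0037
- Power of the two-sided exact McNemar test: 0.793 at n = 67, 0.803 at n = 68, 0.822 at n = 70

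The stated 68 reproduces, so the same calculation is used for the safety test.

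**2. What happens to each kind of garment reactor, with no imputation.**

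| Sequence | Garment | Holter | In McNemar? | In garment percentage? |
|---|---|---|---|---|
| Holter first, stops garment for a reaction | present | already recorded | yes | yes |
| Garment first, reacts, still has Holter | present | recorded | yes | yes |
| Garment first, withdrawn, no Holter | present | missing | **no** | yes |

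Only the third row is lost, and only from the paired test.

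**3. Sensitivity of the p-value.** With d garment-only and no Holter-only reactions, two-sided p = 2 × (1/2)^d.

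- d = 6: 2/64 = 0.031
- d = 5: 2/32 = 0.063

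One lost patient takes the result across the Protocol's 0.05 level.

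**4. Size over a range (assumptions, not document figures).** Assume 70 patients, 35 per sequence (the allocation ratio is not stated), garment reaction rate 10% and Holter rate 0%. Let s be the share of garment-first reactors who never have the Holter.

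- Expected patients lost = 35 × 0.10 × s
- Probability of a usable garment-only pair = 0.10 × (1 − s/2)
- Garment rate among complete pairs = (3.5 + 3.5(1 − s)) / (70 − 3.5s)

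| s | Expected lost | Garment rate in complete pairs | Power of paired test |
|---|---|---|---|
| 0 | 0 | 10.0% | 0.71 |
| 0.25 | 0.9 | 8.9% | 0.58 |
| 0.5 | 1.75 | 7.7% | 0.43 |
| 1 | 3.5 | 5.3% | 0.14 |

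For the same four values of s, other assumed rates give power of:

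- garment 5%, Holter 0%: 0.14, 0.09, 0.05, 0.01
- garment 20%, Holter 0%: 1.00, 0.99, 0.96, 0.71
- garment 10%, Holter 2%: 0.37, 0.27, 0.18, 0.05

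**The case against.** **The percentages still count these patients.** This stands. Analysis on the pattern of the primary endpoint brings in the percentage with exact CI for each device, which needs no pair, and the safety set keeps garment-only patients. A reader might infer that reactions severe enough to stop wear do not count at all. The documents do not support that, because the loss is confined to the paired test.

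**The efficacy dropout rule.** A reader might also infer that this rule carries over to safety, so that the missing Holter is set to present and the pair cancels. The dropout section limits that rule to efficacy analysis and rules out imputation elsewhere, so this reading fails.

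**A garment reaction need not cancel the Holter.** This stands as a limit on size. The Protocol nowhere says that stopping the garment ends participation. The 3-month Holter is an inclusion condition and is described as routine care, and topical treatment for itching is allowed. Patients with an allergic predisposition or past adhesive reactions are excluded, and related wear is reported in 41 patients over 207 person-days without adverse events. Few patients may be affected. A case in which half or more of all garment reactors are lost is an extreme that nothing in the Protocol points to.

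**The reverse loss is possible.** A Holter-first patient who reacts to the adhesive electrode and withdraws before the garment also has no pair, which would favour the Holter. The background section recognises skin symptoms from adhesive electrodes. This stands, and it is why any rule must treat both sequences alike.

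**Safety is not the trial's question.** The Protocol states no safety margin and does not size the trial for safety, and adverse events are observed and reported separately. This lowers the importance of the point, but it does not justify a test that discards patients because of the outcome.

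**Conclusion.** The point holds in a limited form. Under the stated rules, a garment-first patient withdrawn for a garment reaction without a Holter result drops out of the paired safety test, and each such loss pulls that test towards no garment disadvantage. The net direction assumes that losses from garment reactions outweigh losses from Holter adhesive reactions. That is plausible given 14 days of wear against one and the Protocol's own warning, but the documents do not show it.

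The size is unknown because no reaction or withdrawal rates are given. Under the assumed 10% garment and 0% Holter rates, between about one and 3.5 patients would be lost for s from 0.25 to 1. Losses of that order matter to an exact test on so few discordant pairs. The primary endpoint and the per-device skin percentages are unaffected. This is a cheap improvement to the safety analysis, not a threat to the trial's main conclusion.

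**What to change.** Amend the safety endpoint analysis, in the Protocol or the SAP, as follows:

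1. Name as the lead safety result the incidence for each device, with exact 95% CI, among all patients who wore that device, and report wear duration beside it.
2. Keep the exact McNemar's test on complete pairs as supportive, and report how many patients have a result on one device only, by sequence and by whether they reacted.
3. Prespecify a sensitivity analysis of the paired test in which a reaction on the first device with no result on the second counts as a discordant pair, applied in the same way to both sequences.

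The cost is a few sentences and no new data. The downside is that the sensitivity analysis assumes no reaction on a device that was not worn. That cannot be verified, which is why it should not replace the main analysis. The result may be slightly less favourable to the garment.
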